**Fig. 3 Fig3:**
[figure not shown]
Distress Thermometer and Problem List culturally adapted from the National Comprehensive Cancer Network

### Intervention fidelity

For this study, ENABLE-SG will be delivered by a team of three to four health coaches from different healthcare backgrounds (nursing, social work, or allied health). Before deployment, all health coaches will be certified through the Health Coaching for Older Adults program offered by the Nanyang Technological University Singapore [37]. They will also receive ENABLE-SG-specific training, including independent readings, audio recordings demonstrating coaching techniques, study protocols and procedures, and role-play of six training cases. After deployment, the PI and a senior coach will review a random sample of 20% of recorded coaching sessions delivered by each health coach quarterly, using a standardized checklist to ensure fidelity to the coaching protocol. Less than 80% adherence to the study protocol will be grounds for coach remediation. Health coaches will further receive clinical supervision via weekly case discussions with a specialist palliative care nurse clinician, where the team may initiate a formal palliative care referral when appropriate.

### Data collection

At baseline, demographic information and clinical data will be collected from both patient and caregiver participants. Patient-reported outcome measures will be collected every 3 months until death or the end of the study. Caregiver-reported outcome measures will be collected every 3 months until the patient’s death or the end of study, whichever is earlier. All study outcomes are summarized in Table 2. Study team members will administer the questionnaires at in-person visits or over a phone call. A secure REDCap (Research Electronic Data Capture) database will be used to capture and store all data. All study team members performing collection, extraction, and entry of data will be blinded to the participants’ randomized group assignment. Data entry will be cross-checked by an independent study team member to ensure reliability and accuracy.

**Table 2 Tab2:** Overview of study outcomes

Outcome	Participant	Instrument	Measure description	Assessment
***Specific aim 1***				
Health-related quality of life	Patient	FACIT-Pal	46-item measure; quality of life scale (4 domains – physical, emotional, social, and functional well-being) and a palliative care subscale. It has demonstrated internal consistency reliability and validity for persons with advanced cancer.	Baseline, every 3 months for 12 months
Mood	Patient	CES-D	20-item measure; symptom clustered in 4 domains – depressed affect, somatic complaints, positive affect, and interpersonal activity. The scale demonstrated adequate reliability and validity among community dwelling older adults in Singapore.	
Coping strategies	Patient	Brief-COPE	28-item measure; coping strategies in 14 subscales – self-distraction, active coping, denial, substance use, use of emotional support, use of instrumental support, behavioural disengagement, venting, positive reframing, planning, humour, acceptance, religion, and self-blame. This scale has been validated in the cancer population. It has also been used among family caregivers of individuals with dementia in Singapore before.	
Palliative care concerns	Patient	IPOS	Brief measure of palliative care problems, covering physical and psychological symptoms, social and spiritual issues, communication, information needs, and practical concerns. IPOS has been translated to Chinese and validated in Singapore.	
Health state	Patient	EQ-5D-5L	5-item descriptive system measuring 5 dimensions – mobility, self-care, usual activities, pain/ discomfort, anxiety/ depression; a visual analogue scale measuring overall health status. The tool has been validated in Singapore.	Baseline, every 3 months until death or end of study
Healthcare resource utilization	Patient	Electronic medical records	Dates of emergency department visits and hospital admissions, hospital bill size, date of first review by existing palliative care services, date of death, and place of death	Enrolment until death or end of study
***Specific aim 2***				
Health-related quality of life	Caregiver	SCQOLS	15-item measure; quality of life measure covering 5 domains – physical well-being, mental well-being, experience & meaning, impact on daily living, and financial well-being. It has been developed and validated in Singapore.	Baseline, every 3 months, for 12 months
Mood	Caregiver	CES-D	*Same as above*	
Coping strategies	Caregiver	Brief-COPE	*Same as above*	
Satisfaction with care	Caregiver	FAMCARE	10-item unidimensional scale measuring family satisfaction. It has been translated to Chinese and validated in Singapore	
Caregiving costs	Caregiver	Caregiving costs questionnaire	Employment status; productivity loss (hours missed from work, impairment while at work, and impairment in regular activities) due to caregiving	
		Electronic medical records	Dates of emergency department visits and hospital admissions, and hospital bill size	
***Specific aim 3***				
Acceptability	Patient Caregiver	Structured feedback survey	Acceptability, relevance, comfort level, overall satisfaction, and intention to recommend ENABLE-SG to others in similar situations are rated on a 5-point Likert scale	End of study participation
Adoption				
Appropriateness	Patient Caregiver Healthcare provider	Semi-structured interviews	Interview guide developed based on the Consolidated Framework for Implementation Research (CFIR)	≥ 6 months after baseline
Feasibility				
Fidelity	Health coach	Self-reporting checklist, field notes, recordings	Modifications to protocol, discussions from conducted coaching sessions	Throughout study period
Implementation cost	Health coach	Process maps, project records	Identify key intervention activities to elucidate cost of involved personnel and resources through a time-tracking system and an activity-based costing approach	
Penetration	Oncologist	Study records	Number and proportion of approached oncologists who agree for study to be conducted in their clinics	

*Abbreviations*: *Brief-COPE* Brief Coping Orientation to Problems Experienced Inventory, *CES-D* Center for Epidemiological Studies-Depression, *EQ-5D-5L* EuroQOL Group 5-Dimension Health-related Quality of Life Measurement, *FACIT-Pal* Functional Assessment of Chronic Illness Therapy – Palliative, *FAMCARE* Family Satisfaction with End-of-Life Care, *IPOS* Integrated Palliative Care Outcomes Scale, *SCQOLS* Singapore Caregiver Quality of Life Scale

#### Patient- and caregiver-reported outcomes

The primary outcome measure is patient health-related QoL measured using the Functional Assessment of Chronic Illness Therapy – Palliative (FACIT-Pal) at 6 months [38]. Secondary patient-reported outcomes include: (1) mood measured using the Centre for Epidemiological Studies-Depression (CES-D) [39, 40], (2) coping strategies measured using the Brief Coping Orientation to Problems Experienced (Brief-COPE) Inventory [41–45], (3) palliative care concerns measured using the Integrated Palliative Care Outcomes Scale (IPOS) [46], and (4) health status measured using the EuroQOL Group 5-Dimension Health-related Quality of Life Measurement (EQ-5D-5L) at 6 months [47–49]. Caregiver-reported outcomes include: (1) health-related QoL measured using the 15-item Singapore Caregiver Quality of Life Scale (SCQOLS-15) [50, 51], (2) mood measured using the CES-D, (3) coping strategies measured using the Brief-COPE, and (4) satisfaction with care measured using the Family Satisfaction with End-of-Life Care (FAMCARE) Scale [52].

#### Healthcare resource utilization, patient survival, and caregiving costs

The following data will be extracted from administrative and billing data in the electronic medical records for all participants: dates of emergency department visits and urgent hospital admissions, and gross hospital bills. For patients, additional data on the date of first review by existing palliative care services, date of death, and place of death will be extracted. Caregivers will further complete caregiving costs questionnaires during their 3-monthly follow-up on their employment status and productivity loss (hours missed from work, impairment while at work, and impairment in regular activities) due to unpaid caregiving.

#### Implementation outcomes

Proctor et al.’s taxonomy guided the selection of implementation outcomes [53]. The penetration of ENABLE-SG will be assessed by the number and proportion of approached oncologists who agreed to include their clinics for study screening. The acceptability, adoption, appropriateness, and feasibility of ENABLE-SG will be evaluated using a structured feedback survey completed by all participants at the end of study participation (or withdrawal) and semi-structured interviews with a purposive sample of patients, caregivers, and healthcare providers. Purposive sampling will ensure representativeness across ages, genders, cancer types, and the extent of ENABLE-SG completion. These semi-structured interviews will be conducted after the primary outcome measurement at 6 months post-enrolment. The interviewer will use an interview guide (Supplementary File 1) developed based on the Consolidated Framework for Implementation Research (CFIR) [54]. Each interview lasting approximately 30-60 min will be audio-recorded and transcribed verbatim. Recruitment for implementation outcome interviews will stop when data saturation is reached.

Fidelity will be assessed using self-reporting checklists, field notes on a structured template, and sample recordings of coaching sessions completed by each health coach. The weekly clinical supervision sessions will be recorded in field notes. Deviations from the ENABLE-SG protocol and reasons for modification will be deliberated and documented.

Implementation costs will be collected from the healthcare system’s perspective. Fixed set-up costs include health coach training (time, materials, space, supplies, trainer). To identify and value ongoing variable costs, we will develop process maps with health coaches to identify key activities (e.g., preparing, conducting, documenting, supervising, and auditing coaching sessions) to elucidate the personnel and resources involved using an activity-based costing approach [52]. We will record the pay scales of involved personnel and use a time-tracking system to record time spent in training and identified key activities. Time will be valued using hourly wages and fringe benefits at market rates for the services provided. The cost of materials and resources will be tracked and valued using project records or current market prices.

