**Methods:**

This single-centre, assessor-blind, wait-list (immediately vs. 6 months) randomized controlled trial will recruit 300 adult patients within 60 days of an advanced cancer diagnosis and their family caregivers from the National Cancer Centre of Singapore. ENABLE-SG comprises structured psychoeducational sessions with a telehealth coach, covering essential topics of early palliative care. Participants will be assessed at baseline and every 3 months until patient’s death, 12 months (caregivers), or end of study (patients). The primary outcome is patient quality of life 6 months after baseline. Secondary patient-reported outcomes include mood, coping, palliative care concerns, and health status. Secondary caregiver-reported outcomes include caregiver quality of life, mood, coping, and care satisfaction. Mixed-effects regression modelling for repeated measurements will be used. To assess the effectiveness of ENABLE-SG versus usual care, patient and caregiver outcomes at 6 months will be compared. To compare earlier versus delayed ENABLE-SG, patient and caregiver outcomes at 12 months will be compared. Within the hybrid type 1 effectiveness-implementation design, implementation outcomes will be evaluated in both the early and delayed groups. Acceptability, adoption, appropriateness, and feasibility will be assessed using a feedback survey and semi-structured interviews with a purposive sample of patients, caregivers, and healthcare providers. Transcribed interviews will be analysed thematically. Other implementation outcomes of penetration, fidelity, and cost will be assessed using records of study-related processes and summarized using descriptive statistics. A cost-effectiveness analysis will also be conducted.

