## Methods/ design

### Study design

This type 1 hybrid effectiveness-implementation randomized wait-list controlled trial will take place in the outpatient setting at the National Cancer Centre of Singapore (NCCS). NCCS serves 65% of all cancer patients in the public sector in Singapore. Patient participants will be randomized to receive the ENABLE-SG intervention immediately (early ENABLE-SG group) or after 6 months (wait-list control group) (Fig. 1). Caregiver participants will be assigned to the same group as the patient care recipient. Patient participants will be followed up until death or the end of the study, whichever is earlier. Caregiver participants will be followed up until the patient’s death or the end of study, whichever is earlier. Figure 2 depicts the study schedule.

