### Usual care prior to delayed intervention

Patients randomized to the wait-list control group will receive usual care for the 6 months before receiving the ENABLE SG intervention. Under usual care, patients are managed by their primary oncologists who focus on cancer-directed treatments. When patients develop complex care needs, the primary oncologist may refer the patient to available palliative care services. Patients and their caregivers may access usual support services such as medical social worker consultations, allied health professional consultations, and support group participation. Data on the utilisation of these other services will also be collected.

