### ENABLE-SG intervention

ENABLE-SG closely follows the original ENABLE model with some modifications following cultural adaptation: (1) adding optional discussion topics, (2) assessing preferences for decision-making and tailoring sessions to individual family dynamics, and (3) allowing a flexible mode of delivery [32, 35]. Every patient and caregiver will receive six and four individual structured psychoeducational sessions, respectively, with a health coach. These sessions will be primarily delivered over the phone. Different health coaches will conduct sessions for each patient-caregiver dyad. The topics covered in the sessions are based on essential elements of early palliative care (Table 1) [18]. All sessions will begin with screening for distress using the Distress Thermometer and Problem List culturally adapted from the National Comprehensive Cancer Network (Fig. 3) [36]. From screening results, the health coach can flexibly change the order of the topics to address specific problems and discuss additional topics where relevant. The health coach will aim to conduct the sessions weekly. Most participants from the pilot study could complete the sessions within three months.

**Table 1 Tab1:** Topics and elements of palliative care covered by ENABLE-SG sessions

Patients	Caregivers	Topics covered	Elements of palliative care
**Session 1** Maintaining positivity	**Session 1** Maintaining positivity	• Handling problems with a positive attitude • A problem-solving attitude • The seven steps of problem-solving	• Improving symptom relief and function • Psychosocial and spiritual care
**Session 2** Self-care	**Session 2** Self-care	• Healthy eating and nutrition • Exercise • Quitting smoking • Sexuality • Work and family	Improving symptom relief and function
**Session 3** Coping with stress	**Session 3** Coping with stress	• Coping with stress • Spirituality • Getting the support you need	Psychosocial and spiritual care
**Session 4** Managing symptoms	**Session 4** Managing symptoms	• Managing symptoms • Common symptoms in cancer • Common thoughts and feelings	Improving symptom relief and function
**Session 5** Talking about what matters most and making choices	-	• Talking with your family and healthcare providers • Core values: what matters most • Decision aids: making choices that are right for you	Enhancing communication, values-based treatment, and goals of care conversations

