### Data analysis

#### Analysis of effectiveness outcomes

Using an intention-to-treat approach, we will compare ENABLE-SG versus usual care at 6 months post-enrolment. Linear regression will be used to compare each patient- and caregiver-reported outcome between intervention and wait-list control groups, with baseline score as a covariate. The negative binomial regression will be used to compare the number of emergency department visits and number of days spent in hospital(s) during the first 6 months post-enrolment, with an offset term that equals 6 months or time from enrolment to death, whichever is earlier. Using a similar approach, we will compare early ENABLE-SG in the intervention group versus delayed ENABLE-SG in the wait-list control group for abovementioned outcomes at 12 months post-enrolment.

We will also assess between-group differences in outcomes from baseline across all timepoints from enrolment using a mixed-effects regression model for repeated measurements. Time since enrolment will be treated as a discrete variable that interacts with the trial groups [56]. Intervention effects will be estimated at each of the 3-monthly timepoints. The comparisons at 3- and 6-months post enrolment will indicate the effect of ENABLE-SG versus usual care; comparisons after 6 months will shed light on the effect of early versus delayed initiation of ENABLE-SG.

For patients, the date of the first specialist palliative care review will be used to compute the following indicators of the timing of palliative care initiation: (1) number of days from enrolment to first palliative care review; (2) number of days from first palliative care review to death. Survival and the timing of palliative care review initiation will be estimated and compared between trial groups using time-to-event analysis.

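### The acceptability survey is tied to the end of study participation, not of coaching, so patients who die without withdrawing give none and recall length differs by arm

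*Protocol article*

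**What the plan says.** Implementation outcomes names two sources for acceptability, adoption, appropriateness and feasibility. One is a "structured feedback survey completed by all participants at the end of study participation (or withdrawal"). The other is a set of interviews with a purposive sample, held after the 6-month assessment. Table 2, under Specific aim 3, gives the survey timing only as "End of study participation" and lists patients and caregivers as respondents.

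Study design defines when participation ends. For patients: "Patient participants will be followed up until death or the end of the study, whichever is earlier". For caregivers: "Caregiver participants will be followed up until the patient’s death or the end of study, whichever is earlier". The Abstract differs for caregivers, with assessments "every 3 months until patient’s death, 12 months (caregivers), or end of study (patients").

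On the length of coaching, the ENABLE-SG intervention section reports: "Most participants from the pilot study could complete the sessions within three months". Wait-list patients "will receive usual care for the 6 months before receiving the ENABLE SG intervention".

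The article gives no study end date and no maximum follow-up, and it does not tie the survey to the end of coaching. The latest single time point named for a group comparison is month 12: early "versus delayed ENABLE-SG in the wait-list control group for abovementioned outcomes at 12 months post-enrolment".

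**The concern.** The survey asks participants to rate a coaching programme, but its date follows the follow-up schedule. Three consequences come from the stated rule itself:

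- A patient whose participation ends in death cannot fill in a form due at that moment, so the intention to survey everyone cannot be met.
- A patient who stays in answers well after coaching, particularly in the early arm.
- The delay depends on the arm, although the Abstract says that implementation outcomes will be evaluated in both groups. A difference between arms in satisfaction or relevance would be mixed with a difference in recall.

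Aim 3 is one of the two purposes of the hybrid design and is meant to inform scale-up. The planned survey analysis is descriptive, so it would not correct for who answered or how late. Feedback not collected before a patient dies cannot be recovered for that patient.

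**Working it through.** **The plan's own figures.** The article gives no expected survey yield. Its only computed size, for the primary outcome, reproduces: 0.4 SD, 80% power and 5% two-sided need 99 per arm, 198 in all (stated 200), and 300 × (1 − 0.34) = 198. The 34% attrition does not separate deaths from withdrawals, so it cannot be used here.

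**Inputs**
- Coaching takes about 3 months (pilot; ENABLE-SG intervention). It starts at month 0 in the early arm and at month 6 in the wait-list arm, so it ends at about months 3 and 9.
- Month 12 is taken as the earliest planned end of participation (Analysis of effectiveness outcomes).
- Median survival is 1.3 years (15.6 months) for stage 4 and more than 4 years for stage 3 (Discussion). I use 48 months for stage 3.
- Assumptions: exponential survival, with the clock starting at enrolment. Stage mix and study end date are unknown, so results are ranges.

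**Recall gap** = survey month − month coaching ends.
- At month 12: early 12 − 3 = 9 months; wait-list 12 − 9 = 3 months.
- Any later study end lengthens both gaps equally and leaves the 6-month difference between arms.

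**Share alive** S(t) = 0.5^(t/median), t in months.

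| Month | Median 15.6 months | Median 48 months |
|---|---|---|
| 3 | 0.875 | 0.958 |
| 6 | 0.766 | 0.917 |
| 12 | 0.587 | 0.841 |

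- Dead by month 12: 1 − 0.587 = 41%, or 1 − 0.841 = 16%. Of 150 per arm, about 62 or 24.
- Dead by month 6, before interviews open: 23% or 8%.
- Dead between months 3 and 6: 0.875 − 0.766 = 11%, or 0.958 − 0.917 = 4%. In the early arm these patients would typically have finished coaching. Unless they withdrew first, they would enter neither the survey nor the interviews.

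**Loss that matters in the wait-list arm.** Patients who die before month 6 have had no coaching to rate. The relevant deaths are those between months 6 and 12: 0.766 − 0.587 = 18% of those randomized, or 0.917 − 0.841 = 8%.

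**Effect of surveying when coaching ends.** With a constant hazard, the share dying within 3 months of starting coaching is the same in both arms: 1 − 0.875 = about 12%, or 1 − 0.958 = about 4%. Some loss remains, but less than the 16% to 41% by month 12 in the early arm, and recall would be short in both arms.

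**The case against.** **Only survivors are sampled.** A reader might infer this, but the rule also triggers the survey at withdrawal. A patient who deteriorates and withdraws is surveyed on leaving, so the death percentages are upper limits on what is lost to death. This stands.

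**The survey is late for everyone.** Not shown. At month 12 the wait-list gap is only about 3 months; the long gap is firm for the early arm alone.

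**Most patients are lost.** Applying the stage 4 median to all patients at 24 months gives 66% dead. However, stage III disease is eligible, a 4-year median gives 29%, and no 24-month horizon appears in the article. Because the stage 3 median is stated as above 4 years, even 16% at month 12 is on the high side for that stage.

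**The implementation findings as a whole are biased.** Too broad. Fidelity, penetration and cost do not use the survey. The interviews do not wait for study end and seek a spread in the extent of completion. Caregivers can answer after a patient's death. These sources help only in part: about 15 patients are expected for interview, none before month 6, and not every patient has an enrolled caregiver. The Abstract and Study design also disagree on when caregiver participation ends.

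**People never coached will rate the programme.** As worded, the survey also reaches wait-list patients who withdraw before month 6. The instrument is not shown and may route them past such items, so this is a reason to state the respondents, not a demonstrated error.

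**Late timing protects blinding.** Under Data collection, staff who collect and enter data are blinded, and a survey at the end of coaching would reveal the arm to them. The article does not give this reason, but it is sound and the fix must respect it.

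**Conclusion.** The point holds, with limited reach. The article fixes the survey at a time when patients who die without withdrawing cannot answer. Those who remain answer about 9 months or more after coaching in the early arm and about 3 months or more in the wait-list arm. By month 12 about 16% to 41% of patients would have died, under exponential survival from enrolment and the article's two medians. The true survey loss depends on stage mix, study end date and how many withdraw first, none of which is given. Reading the end of participation as month 12, when most patient questionnaires stop in Table 2, does not remove the problem, since these figures already use month 12.

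The effect falls on one descriptive Aim 3 outcome. The primary outcome, its analysis and the sample size are unaffected. The change is worth making because it is cheap and the feedback of patients who die cannot be obtained later.

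**What to change.** In Implementation outcomes and in Table 2:

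- Trigger the survey at the last coaching session or when coaching is discontinued, including by withdrawal, in both arms.
- Limit it to participants who had at least one session.
- Collect it by self-completion, so that blinded data collectors are not involved.
- Report the response rate by arm and by vital status.

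Fixed survey dates after the month-6 assessment (early arm) and the month-12 assessment (wait-list arm) would be a weaker choice. They would still miss wait-list patients who die between months 6 and 12.

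The cost is a minor amendment to survey timing and schedule, with no extra staff. Participants enrolled before the change will have mixed timing. Recruitment began in December 2023, so an early change keeps that group small. Patients who die during coaching may still be missed.
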